
**Figure 1 F1:**
[figure not shown]
The flow chart of this trial.

### Participants

2.2

#### Inclusion criteria

2.2.1

Diagnosis of lumbar disc herniation (LDH) according to established diagnostic criteria (25), confirmed by MRI showing disc protrusion, extrusion, or sequestration at L3/4, L4/5, or L5/S1 levels. Mild-to-moderate degenerative changes (Pfirrmann grade ≤ III) in the absence of significant nerve root compression do not exclude participation.Age ≥ 20 and ≤ 55 years, regardless of sex (3, 26).Duration of the disease ≥ 3 months (27, 28).Visual Analog Scale (VAS) score ≥ 3 and ≤ 6 (29).Provision of written informed consent, voluntary agreement to participate, and ability to comply with the treatment protocol.

#### Exclusion criteria

2.2.2

Presence of other serious diseases, such as tumors, fractures, infections, or tuberculosis.Spinal deformities, severe spinal trauma, or a history of spinal surgery.Severe osteoporosis (T-score ≤ –2.5), ankylosing spondylitis, or acute vertebral fracture.Women who are pregnant or breastfeeding.Individuals with psychiatric disorders, significant physical disabilities, or cognitive impairments.Current or anticipated receipt of any concomitant treatments (e.g., medication, surgery, or alternative rehabilitation therapies) during the study period.

#### Withdrawal criteria

2.2.3

Failure to complete the treatment according to the study protocol after enrollment.Poor compliance during the trial, including modification of the treatment protocol or receipt of other related therapies.Withdrawal from the study at the participant's request or termination of participation during the trial.

**Note:** Participants who withdraw from the intervention will still be encouraged to complete follow-up assessments whenever possible. All randomized participants will be included in the intention-to-treat analysis regardless of adherence.

#### Termination criteria

2.2.4

The participant experiences serious adverse events related to the treatment intervention.Severe complications or significant deterioration of the disease occur during the study period.The investigator determines that the participant meets the criteria for trial termination according to the standard operating procedures, and the intervention should be stopped immediately.

### Randomization

2.3

Participants will be randomly assigned in a 1:1:1 ratio to three groups in this single-center trial. A total of 96 patients with LDH who met the eligibility criteria will be enrolled and randomly allocated in a 1:1:1 ratio to the Tuina group, the core stability training group, or the combined Tuina plus core stability training group. The randomization sequence will be generated by an independent researcher using SPSS statistical software (version 27.0.1; IBM Corp., Armonk, NY, USA). To ensure allocation concealment, the random sequence numbers will be placed in sequentially numbered, opaque, sealed envelopes. Participants who meet the inclusion criteria and provide written informed consent will receive the envelopes in the order of recruitment, and the envelopes will be opened prior to the intervention to determine group assignment.

### Blinding

2.4

In this study, blinding will be implemented for outcome assessors and data analysts. Group allocation will be coded to ensure objectivity during the evaluation and analysis processes. Due to the nature of the interventions, blinding of therapists and participants will not be feasible.

#### Objective outcomes

2.4.1

(Musculoskeletal ultrasound, MRI, X-ray, and pressure biofeedback unit) will be assessed by independent researchers who are blinded to group allocation and not involved in the intervention delivery.

#### Patient-reported outcomes

2.4.2

(Visual Analog Scale, Oswestry Disability Index, Japanese Orthopedic Association score, and 36-Item Short Form Health Survey) are inherently subjective and cannot be blinded, as participants are aware of their treatment assignment. Therefore, these outcomes are at risk of detection bias, which will be acknowledged as a limitation. Statistical analyses will be performed without knowledge of the actual group assignments, and unblinding will occur only after completion of all statistical analyses. Premature unblinding will not be permitted unless serious adverse events or other emergencies occur.

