#### Adverse events

2.7.3

All adverse events occurring during the intervention and follow-up period will be recorded and monitored, including but not limited to: increased local pain, muscle soreness, fatigue, skin abrasion or ecchymosis from Tuina, and exacerbation of radicular symptoms. Any discomfort or unexpected events will be documented in detail, including their type, severity, duration, and management. The relationship between adverse events and the intervention will be evaluated. Serious adverse events will be reported immediately to the ethics committee, and appropriate medical management will be provided. If necessary, the trial will be terminated to ensure participant safety.

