#### Intervention delivery and fidelity

2.8.1

All interventions will be delivered by licensed practitioners with at least 3 years of clinical experience. Prior to trial initiation, all practitioners will undergo standardized training and pass a clinical trial operation assessment to ensure consistency in intervention delivery, including treatment intensity, frequency, and procedures according to the study protocol.

All Tuina treatments will be delivered by the same licensed Tuina practitioner, and all core stability training sessions will be supervised by the same licensed rehabilitation therapist throughout the study. Although therapist blinding is not feasible due to the nature of the interventions, therapists will strictly follow standardized treatment manuals and will not be involved in outcome assessment, data collection, or statistical analysis.

To ensure protocol adherence and minimize variability in treatment delivery, regular supervision sessions will be conducted throughout the study. Treatment fidelity will be monitored using a standardized checklist (Supplementary Table S2) and periodic supervision. In addition, a random sample of treatment sessions will be independently observed or recorded for fidelity evaluation. Adherence to the intervention protocol will also be documented throughout the study.

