### Statistical analysis

2.11

All statistical analyses will be performed using IBM SPSS Statistics (Version 27.0). Efficacy analyses will follow the intention-to-treat (ITT) principle, including all randomized participants. Continuous variables will be tested for normality and presented as mean ± standard deviation or median (interquartile range), as appropriate, while categorical variables will be expressed as counts and percentages. Baseline characteristics will be summarized descriptively without formal statistical comparisons. Primary and secondary outcomes will be analyzed using linear mixed-effects models, with group, time, and group-by-time interaction as fixed effects and subjects as random effects. Intervention duration (20 vs. 40 min) and baseline values of the outcome measures will be explicitly included as covariates to account for potential confounding effects. Therapist identity will be included as a random intercept to account for potential clustering effects. Model assumptions will be evaluated using residual diagnostics. If significant group-by-time interactions are detected, post-hoc pairwise comparisons with Bonferroni correction will be performed. Missing data will be handled using multiple imputation under the missing-at-random assumption. Safety analyses will include all participants who received at least one treatment, and adverse events will be compared using the chi-square test or Fisher's exact test, as appropriate. Sensitivity analyses, including complete-case analyses, per-protocol analyses, and analyses adjusted for intervention duration, will be conducted to assess the robustness of the primary outcome. All statistical tests will be two-sided, with a significance level set at *P* < 0.05, and 95% confidence intervals will be reported. Effect sizes (e.g., Cohen's d) will also be reported to facilitate interpretation of the clinical relevance of the findings.

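### The session-duration covariate reveals the combined arm to an analyst who is meant to be blind to allocation

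*Protocol article*

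**What the plan says.** **The promise.** Section 2.4.2 states: "Statistical analyses will be performed without knowledge of the actual group assignments, and unblinding will occur only after completion of all statistical analyses". The Abstract, section 2.1 and section 2.4 make the same claim. The Discussion lists blinded data analysis as a strength and offers it as partial mitigation for the unblinded participants and therapists. The only masking device described is in section 2.4: "Group allocation will be coded to ensure objectivity during the evaluation and analysis processes".

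**The model.** Section 2.11 specifies linear mixed-effects models for the primary and secondary outcomes and adds two terms to group and time:

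- "Intervention duration (20 vs. 40 min) and baseline values of the outcome measures will be explicitly included as covariates"
- "Therapist identity will be included as a random intercept to account for potential clustering effects"

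The same section lists a duration-adjusted analysis among the sensitivity analyses. Section 2.6.3 and the Discussion also rely on the duration covariate.

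**How the two variables relate to arm.** Sessions last about 20 minutes in the Tuina arm (2.6.1), about 20 in the core stability arm (2.6.2) and about 40 in the combined arm (2.6.3). Section 2.8.1 fixes one provider per modality for the whole trial: "All Tuina treatments will be delivered by the same licensed Tuina practitioner, and all core stability training sessions will be supervised by the same" therapist. The combined arm receives both modalities in one session, and so sees both providers.

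**The concern.** Coding the arms keeps an analyst blind only if nothing else in the analysis file is a label for arm. Here the prescribed model calls for two variables that are set by arm. One of them, duration, has a value found only in the experimental arm.

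The combined arm is in both comparisons that bear on the trial's question: combined against Tuina, and combined against core training. An analyst who knows which code is the combined arm knows which direction of each contrast favours the hypothesis. Analyst blinding exists to protect any choice made after the data are seen. The article does not show how many such choices remain open. It does advertise the safeguard repeatedly, and a reader of the trial report would rely on it.

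**Working it through.** **Inputs**

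- Allocation 1:1:1 to three arms (2.3). Size: 27 per group, 15% dropout, 32 per group, 96 in total (2.5).
- Nominal session length: Tuina 20, core training 20, combined 40 minutes (2.6.1 to 2.6.3).
- Providers: Tuina arm, the Tuina practitioner; core arm, the rehabilitation therapist; combined arm, both (2.6.3, 2.8.1).

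**The plan's own figure.** For a two-sample t-test with d = 0.78 and two-sided alpha 0.05, power is 0.788 at 26 per group and 0.803 at 27, so 27 is right. Then 27 / (1 − 0.15) = 31.8, rounded up to 32, and 3 × 32 = 96. The arm sizes reproduce.

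**What the analyst can deduce.** Call the coded groups A, B and C. There are 3! = 6 ways to match them to the three true arms. Each variable in the file rules some of these out.

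| In the analyst's file | Labelings left | Participants whose arm is known |
|---|---|---|
| Group codes only | 6 | 0 of 96 |
| + duration as 20/40 | 2 | 32 of 96 (combined) |
| + duration, values disguised | 2 | 32 of 96 (combined) |
| + duration and masked therapist codes | 2 | 32 of 96 (combined) |
| + duration and unmasked therapist identity | 1 | 96 of 96 |

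- *Duration.* The group with 40 must be the combined arm. The other two groups can be matched in 2! = 2 ways. Recoding the values does not help: two groups share a level and one has a level to itself, so the odd one out is still the combined arm.
- *Therapist identity, unmasked.* Among the two 20-minute groups, one lists the Tuina practitioner and the other the rehabilitation therapist. One labeling remains, and 32 + 64 = 96.
- *Therapist identity, masked.* The analyst sees that the two single-therapy arms have different providers but not which is which. Those 64 stay unnamed. If both providers are recorded for the combined arm, masked codes alone (without duration) still single it out.

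**Does removing the terms lose anything?** Nominal duration equals 20 + 20 × (indicator of the combined arm). A design matrix with intercept, two group indicators and duration has 4 columns and rank 3, so duration cannot be estimated separately from group. Which provider or providers a participant sees is likewise fixed by arm.

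**The case against.** **Therapist labels may be masked.** A random intercept works equally well with pseudonymous codes, and how identifiers are labelled in the file is a detail that an article may leave to fuller documents. This stands. A reader might infer that all 96 allocations are certain to be known. That is the natural reading of section 2.11, which speaks of identity and mentions no masking, but the document does not settle it. What is certain is 32.

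**Adverse events.** A reader might add that events such as "skin abrasion or ecchymosis from Tuina" (section 2.7.3) also reveal arm. The support is weak. The list is illustrative, nothing places such entries in the efficacy file, and Tuina is given in two of the three arms, so an event of this kind does not name an arm.

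**No bias is shown.** This is correct. Responses to residual diagnostics, the imputation model and the per-protocol set may be fixed in an analysis plan that is not at hand, and section 2.10 locks the database before analysis. The finding is that a stated design property fails, not that a result will be distorted.

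**It is a by-product of aliasing.** In part, yes. The two terms should go in any case because they cannot be separated from treatment. The blinding claim still needs its own check, because anyone who defends keeping the covariate gives up that claim.

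**Conclusion.** The concern holds in this form: the duration covariate exposes the combined arm, 32 of 96 participants, under any coding. This contradicts the promise that all analyses precede unblinding. The number rises to as many as 96 of 96 only if therapist identity reaches the analyst unmasked.

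The conclusion rests on two assumptions. Duration enters as the nominal 20 or 40 minutes, as section 2.11 writes it, and the person who fits the model is the blinded analyst.

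A reader might extend the point to the outcome assessors or to the trial's error rates. The documents do not support that. Assessors do not fit the model, and the blinded assessment of objective outcomes in section 2.4.1 stands. Sample size, alpha and power do not change. The matter should be put right before analysis, but it does not undermine the randomised comparison.

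**What to change.** 1. In section 2.11, remove session duration and therapist identity from the model, and keep both out of the analyst's file. Arm determines both, so no separable information is lost.
2. Delete the duration-adjusted sensitivity analysis in 2.11 and the statements in 2.6.3 and the Discussion that duration will be a covariate. Editing 2.11 alone would leave these in contradiction. The Discussion can keep its acknowledgement that the combined arm receives twice the session time.
3. Supply arms as A/B/C until the primary and secondary efficacy outputs are locked, and word 2.4.2 to match. Adherence data need not be withheld.
4. If either variable is kept, withdraw or qualify the claim of analyst blinding in the Abstract, 2.1, 2.4 and the Discussion.

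The cost is wording in several sections and a small data-management step to prepare the coded file. No participant procedure or sample size changes.

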### Sample size calculation

2.5

The sample size was calculated using G*Power 3.1. The calculation was based on the primary outcome, namely the muscle activation ratio of the transversus abdominis assessed by musculoskeletal ultrasound. Previous studies in patients with low back pain have reported medium-to-large effect sizes (Cohen's d ≈ 0.71) for changes in transversus abdominis activation following core stability training (30). Furthermore, ultrasound studies in patients with LDH have demonstrated significant alterations in core muscle morphology (31), suggesting that similar or larger effects may be anticipated in this population. Therefore, a conservative effect size of 0.78 was assumed for the present study.The selected effect size was based on previous studies reporting moderate-to-large effects in similar populations and was conservatively estimated.

With a two-sided α of 0.05 and a power (1−β) of 0.80, the required sample size was 27 participants per group. Considering a 15% dropout rate, the final sample size was set at 96 participants, with 32 participants in each group.

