Current clinical practice guidelines recommend Tuina therapy and exercise-based rehabilitation as important nonsurgical interventions for LDH (6, 11). Tuina, a traditional manual therapy, has been shown to relieve pain and improve functional outcomes, potentially through mechanisms such as enhancing local circulation, reducing inflammation, and modulating neural activity (12). The Tuina protocol applied in this study primarily targets the Dai meridian region, which anatomically corresponds to the lumbar–abdominal musculature and thoracolumbar fascia. Acupoints such as Daimai (GB26), Wushu (GB27), and Weidao (GB28) are anatomically located along the lateral abdominal wall, corresponding to the external oblique, internal oblique, and transversus abdominis muscle layers. These points have been widely selected in clinical and experimental studies based on their relevance to abdominal musculature and their role in modulating lumbar stability and core function (13).Previous studies from our research group have demonstrated that abdominal Tuina can increase transversus abdominis thickness and improve lumbar function (14, 15). However, existing evidence suggests that while Tuina is effective in alleviating pain and improving physical function, its effects are primarily limited to symptomatic relief, with insufficient influence on deep muscle activation and neuromuscular control, which are essential for long-term spinal stability (9, 16).

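### Section 2.5 calls d = 0.78 conservative when its only cited effect is about 0.71, so the stated 80% power needs restating, also at the Bonferroni level and for the combined-versus-core contrast

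*Protocol article*

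**What the plan says.** Section 2.5 ties the sample size to the transversus abdominis (TrA) activation ratio: "The calculation was based on the primary outcome, namely the muscle activation ratio of the transversus abdominis assessed by musculoskeletal ultrasound". The one numerical effect given is a Cohen's d of about 0.71, reported in low back pain "for changes in transversus abdominis activation following core stability training". The section then refers to ultrasound findings of altered muscle morphology in lumbar disc herniation, "suggesting that similar or larger effects may be anticipated in this population", with no figure attached. It concludes: "Therefore, a conservative effect size of 0.78 was assumed for the present study". The next sentence again describes the value as conservatively estimated.

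The calculation follows: "With a two-sided α of 0.05 and a power (1−β) of 0.80, the required sample size was 27 participants per group". Then: "Considering a 15% dropout rate, the final sample size was set at 96 participants, with 32 participants in each group".

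Four other places bear on this:
- The Introduction sets the question as whether the combination beats either therapy alone.
- Section 2.6.3 gives the combined arm Tuina followed by the same core training that the core arm receives.
- Section 2.11 tests pairs of arms with Bonferroni correction if the group-by-time interaction is significant.
- On Tuina's effect on the muscle behind the primary outcome, the Introduction says its effects are mainly symptomatic, "with insufficient influence on deep muscle activation and neuromuscular control". The sentence before reports that abdominal Tuina can thicken the TrA.

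**The concern.** A conservative planning effect lies at or below the evidence. Here it lies above the only estimate quoted. A remark that effects may be similar or larger could justify an optimistic choice, but not that word.

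There is also a mismatch of contrast. The 0.71 concerns change after core training. Core training is given in both the core arm and the combined arm, so the difference between those arms is whatever Tuina adds. Section 2.5 does not name the contrast for which 0.78 was assumed, and the document gives no effect size for combined versus core training or for combined versus Tuina.

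A reader will take 27 completers per arm as 80% power for the trial's question. If the true power for combined versus core training is lower, a non-significant result could be misread as showing that adding Tuina brings nothing.

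**Working it through.** **Inputs.** From section 2.5: d = 0.78 assumed, d ≈ 0.71 cited, two-sided alpha 0.05, power 0.80, 15% dropout, 27 per group before dropout and 32 after. From section 2.11: Bonferroni-corrected pairs. The document does not state the number of pairs; three arms give three, so alpha = 0.05/3 = 0.0167.

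**Method.** Two-sample t-test with n per group: df = 2n − 2, noncentrality δ = d·√(n/2), and power = P(|T| > t at 1 − α/2) with T noncentral t(df, δ).

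**Step 1: reproduce the plan.** For n = 27 and d = 0.78, δ = 0.78 × √13.5 = 2.87, the critical value on 52 df is 2.007, and power is 80.3%. With n = 26 it is 78.8%, so 27 is the smallest n. Dropout: 27/0.85 = 31.8, rounded up to 32 per arm; 3 × 32 = 96. The plan's figures reproduce.

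The section does not name the test. A three-group ANOVA with a largest pairwise difference of 0.78 gives 25 per group (one arm differs) or 33 (middle arm halfway). Reading 0.78 as Cohen's f gives 7. A one-sided t-test gives 22. Of these readings, only the single two-sided, two-group t-test gives 27.

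**Step 2: the cited effect.** For n = 27 and d = 0.71, δ = 0.71 × √13.5 = 2.61 and power is 72.6%. If nobody drops out, n = 32, δ = 0.71 × √16 = 2.84 and power is 79.8%. Reaching 80% at 0.71 takes 33 completers per arm; 33/0.85 = 38.8, so 39 per arm and 117 in total, against 96.

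**Step 3: the planned pairwise test.** At alpha 0.0167 the critical value on 52 df rises to 2.474. The smallest d detectable with 80% power at n = 27 is then about 0.91, against about 0.78 at alpha 0.05.

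**Step 4: combined versus core training.** The document gives no increment. The values 0.3 to 0.5 below are assumptions that show how power depends on it.

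| d | Basis | Power, n = 27, alpha 0.05 | Power, n = 27, alpha 0.0167 |
|---|---|---|---|
| 0.78 | assumed in 2.5 | 80% | 65% |
| 0.71 | cited in 2.5 | 73% | 56% |
| 0.5 | assumed increment | 44% | 27% |
| 0.4 | assumed increment | 30% | 17% |
| 0.3 | assumed increment | 19% | 9% |

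No figure in the table takes credit for adjustment for the baseline value.

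**The case against.** **The arithmetic is right and the 80% is conditional.** This stands. A reader might infer that the power statement is simply false. It is not: at d = 0.78 in one unadjusted t-test the power is 80.3%. What fails is the justification of the input and the match to the planned comparison.

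**The loss at 0.71 is modest.** Partly right. It is about 7 percentage points with the plan's own 15% dropout, and almost nil if all 32 are evaluable. Section 2.11 also adjusts for baseline, which could recover power. If 0.71 is scaled to the outcome's standard deviation (not stated) and the baseline correlation is 0.3 to 0.5 (an assumption), the effective d is 0.71/√(1 − 0.3²) = 0.74 to 0.71/√(1 − 0.5²) = 0.82. Power with 27 per arm at alpha 0.05 is then about 76% to 84%. But section 2.5 gives no correlation and claims no such gain, and this does not touch the contrast problem.

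**The plan never says that Tuina adds 0.78 on top of core training.** Correct. A reader might infer that it does, but section 2.5 names no contrast. Combined versus Tuina is also a target, and there the added component is core training, to which the cited effect is at least relevant.

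**The documents do not show that Tuina adds little.** Also correct. The Introduction reports TrA thickening with abdominal Tuina and proposes synergy, alongside the remark about insufficient influence on deep muscle activation. Thickness is not the activation ratio, but the evidence cited is mixed. One cannot conclude that combined-versus-core power is far below 80%, only that nothing cited supports 0.78 there.

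**Misreading is partly guarded against.** Section 2.11 promises confidence intervals and effect sizes, and the Discussion concedes a relatively small sample. Neither says how a non-significant combined-versus-core result will be read.

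**Conclusion.** The concern holds in this form. Calling 0.78 conservative is wrong on the section's own figures. Power is 80% only at d = 0.78 in a single two-group t-test at 0.05. It is 72.6% at the cited 0.71 with 27 completers per arm. For the pairwise tests that section 2.11 plans, it is 65% at 0.78 and 56% at 0.71, assuming three pairs and no gain from baseline adjustment. So even on the plan's own effect size, the 80% does not carry over to the corrected comparisons unless baseline adjustment makes up the gap.

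For combined versus core training, the cited effect describes a component common to both arms and gives no support for 0.78. How far power falls there is unknown; the figures for d = 0.3 to 0.5 illustrate the dependence and are not estimates.

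**What to change.** Keep N = 96 and rewrite section 2.5:

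1. Delete both uses of conservative, and state that 0.78 exceeds the cited 0.71.
2. Name the contrast and the test for which 27 per arm was calculated.
3. State power with 27 completers per arm at 0.78 and 0.71, at alpha 0.05 (80% and 73%) and at the Bonferroni level (65% and 56%). Quoting only the 73% would still misstate power for the planned comparisons. If credit for baseline adjustment is wanted, give the assumed correlation and its source.
4. Show combined-versus-core power as conditional on an assumed increment: for d = 0.3, 0.4 and 0.5, 19%, 30% and 44% at 0.05, and 9%, 17% and 27% at 0.0167.
5. State that a non-significant combined-versus-core result will be interpreted from its confidence interval and not as evidence of no benefit.

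The cost is the rewording of one section, with no extra patients and no change to treatment or analysis. The downside is that the stated power becomes less favourable.
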